## **Hypotheses**

Hypotheses regarding the primary study outcomes are:

1. Patients' will be significantly more satisfied with the informed consent and opt-out plus consent procedures than with the opt-out consent procedure
2. Most patients will prefer the opt-out plus consent procedure, the lowest proportion of patients will prefer the opt-out consent procedure.
3. Significantly more patients will be aware of storage of tissue and research use in the informed consent and opt-out plus procedures than in the opt-out procedures.
4. Consent rates will be highest in opt-out and opt-out plus.
5. Members of the medical staff will be most satisfied with and prefer the opt-out and opt-out plus procedures.

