## **Outcomes**

The primary study outcomes will be used to determine which consent procedure serves the needs of patients, clinicians and scientific research best. If one of the three consent procedures serves the needs of all three of these parties best, we will conclude that this consent procedure is the best candidate to become the standard procedure in the Netherlands that prescribes whether and how patients should be asked consent for the use of residual tissue. If the needs of these three parties are best served by different consent procedures, or if it is unclear which consent procedure serves the needs of one or more of the parties best, we will organize an invitational conference in which we invite different stakeholders, such as clinicians, patient organizations and researchers, to discuss how to translate our research findings into clinical practice.

Which consent procedure serves a party's needs best will be decided along the following lines:

- For patients: satisfaction with the received information in the 'best procedure' should be significantly higher than in the consent procedure with the lowest satisfaction rates. Further, the consent procedure should have the highest preference rates among respondents, with a minimum of a 10% difference with the consent procedure with the lowest preference rate. Additionally, the proportion of patients aware of storage of tissue and research use should be at least as high as in the other two groups.

- For clinicians: satisfaction with the received information in the ‘best procedure’ should be significantly higher than in the consent procedure with the lowest satisfaction rates. Further, the consent procedure should have the highest preference rates among participating clinicians and nurse practitioners, with a minimum of a 10% difference with the consent procedure with the lowest preference rate. Additionally, more than 75% of the responding medical staff should indicate that the consent procedure ‘never’ or ‘seldom’ interferes with giving clinical information.
- For research: consent rates for the procedure for which patients and/or clinicians have the highest preference should be at least as high as consent rates in the two other procedures.

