### ***Sample size, statistical power***

Sample size is based on an expected response of 75%, allowing sufficient power to address the major outcomes, i.e. consent rates and preferences for procedures, in different subgroups of e.g. hospitals, age and gender. In order to test the hypothesis that the two interventions result in a difference of at least 10% in consent rates, 0.1% non-consent in the opt-out plus or opt-out group versus 10% in the informed consent group, 121 patients per group are needed (80% power and a 2-sided alpha of 0.05; with continuity correction). The difference of 10% is based on our earlier research and the difference is considered a relevant loss of patient materials for research which may lead to selection bias. Because the setting of diagnosis and treatment is different between surgical and outpatient settings and also between general and academic hospitals, it is important to be able to compare the responses in these subgroups. We have also shown in our earlier studies that educational level is associated with preference for a certain procedure and this may also drive response rates of patients. Therefore we propose to include in each intervention group up to 600 patients to be able to conduct subgroup analysis and include adjustment factors; with a response rate of 75% and hence with 450 participants per group we could stratify for 3 to 4 factors, i.e. 90-150 per subgroup, and still have enough power to investigate a difference in response rate of 0.1% versus 10%. Patients will not be stratified by education or sex; we expect these two factors to be equally distributed across groups.

Another reason to obtain a large sample size is that the percentage of non-consenters is small, while it is important to assess their opinions and reasons for non-consent. In the earlier intervention study, 4.6% of respondents indicated in the questionnaire that they wanted to withhold consent or that they did not know whether they wanted to. A sample size of 1800 patients and a response rate of 75% will lead to approximately 62 patients who want to withhold consent or are not sure which choice to make.

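### The rule for naming the best consent procedure gives no margin for consent and awareness, tests satisfaction only against the lowest procedure, and swaps the satisfaction outcome

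*Protocol*

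**What the plan says.** The rule is in the Protocol, Outcomes. A procedure that serves patients, clinicians and research best is declared the best candidate for a national standard. The criteria are of three kinds.

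- **Consent and awareness (ranking against both others).** The research criterion concerns the procedure that patients, clinicians or both favour, and its wording ends "have the highest preference should be at least as high as consent rates in the two other procedures". For patients, "the proportion of patients aware of storage of tissue and research use should be at least as high as in the other two groups". No test, margin or interval is attached to either.
- **Satisfaction (test against the lowest).** For patients and for clinicians, satisfaction with the information received "should be significantly higher than in the consent procedure with the lowest satisfaction rates".
- **Preference (highest rank plus a gap to the lowest).** The procedure must rank first, "with a minimum of a 10% difference with the consent procedure with the lowest preference rate".

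There is a fallback when the parties' needs point to different procedures, and also "if it is unclear which consent procedure serves the needs of one or more of the parties best, we will organize an invitational conference".

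Three other sections bear on the rule. Hypotheses states that "Consent rates will be highest in opt-out and opt-out plus", and that "Significantly more patients will be aware of storage of tissue and research use in the informed consent and opt-out plus procedures" than under opt-out. Sample size, statistical power uses one shared non-consent rate of 0.1% for opt-out and opt-out plus against 10% for informed consent, and says of the 10-point gap that "the difference is considered a relevant loss of patient materials for research which may lead to selection bias". Study objectives lists patients' satisfaction with a consent procedure, not with information, as the primary outcome.

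**The concern.** The rule produces the trial's headline conclusion, so its behaviour under the protocol's own expectations matters.

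First, the protocol expects opt-out and opt-out plus to share the top place on consent, and groups informed consent with opt-out plus on awareness. If two procedures are truly tied, a requirement to rank no lower than the other, with no tolerance, is settled largely by chance. The protocol regards 10 points as a relevant loss of material, yet a difference of one returned form could decide the consent criterion.

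Second, a satisfaction test against the lowest procedure says nothing about the third. A candidate may pass while another arm is significantly more satisfactory.

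Third, satisfaction with the information received is a different quantity from the primary outcome. Under The intervention, the control arm receives usual care and may read the hospital's general leaflet, while the other two arms get a spoken text and a specific leaflet. On that measure the control arm is likely to come last because of what it was given, which makes the test against the lowest easier for either active arm. The same wording is used for clinicians, who give the information rather than receive it.

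**Working it through.** The protocol gives no probability of any procedure meeting the rule, so there is no figure of its own to reproduce here. Its nearby figure of 121 per group for 0.1% versus 10% matches 90% power; 95 per group suffice at the stated 80%. That is a separate matter and does not affect this point.

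**Inputs from the protocol.** 1800 patients in three equal arms, so 600 per arm; 75% response, so 450 per arm; non-consent 0.1% in both opt-out arms and 10% in informed consent; earlier satisfaction 82% (informed consent) and 65% (opt-out plus).

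**Assumptions.** Consent is counted on all 600; awareness is 80% in both active arms and clearly lower in controls; consent and awareness are independent; satisfaction is 50% in controls.

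**1. Consent, literal reading.** For two arms with the same true rate, P(candidate at least as high) = (1 + P(tie)) / 2. Non-consenters per arm are Binomial(600, 0.001), mean 0.6. P(tie) = 0.4198, so the probability is (1 + 0.4198) / 2 = 0.71. Against informed consent at 90% consent, opt-out plus passes practically always. With 450 per arm the result is 0.75. With both opt-out arms at 1% non-consent and 600 per arm it is 0.56.

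**2. Awareness, literal reading.** For two Binomial(450, 0.8) counts, P(tie) = 0.0332, so the probability is (1 + 0.0332) / 2 = 0.52. For equal awareness anywhere from 50% to 90% it stays between 0.51 and 0.52.

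**3. Both together.** 0.71 × 0.517 = 0.37. An opt-out plus that is truly tied for best on both criteria fails at least one of them in about 63% of trials.

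**4. Satisfaction, 450 per arm (illustration).** Opt-out plus at 65% against controls at 50%: pooled 0.575, z = 0.15 / √(2 × 0.575 × 0.425 / 450) = 4.55, so it passes (power over 99%). Informed consent at 82% against opt-out plus at 65%: pooled 0.735, z = 0.17 / √(2 × 0.735 × 0.265 / 450) = 5.78. The rule never looks at this second contrast.

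**5. A margin-based version (two-sided 95% interval, normal approximation).** Power = Φ((margin + true difference) / SE − 1.96).
- Consent, illustrative 5-point margin, 1% versus 0.1% non-consent, 600 per arm: SE = √((0.01 × 0.99 + 0.001 × 0.999) / 600) = 0.00426; (0.05 − 0.009) / 0.00426 − 1.96 = 7.66; power above 99%.
- Awareness, illustrative 10-point margin, both 80%, 450 per arm: SE = √(2 × 0.8 × 0.2 / 450) = 0.0267; 0.10 / 0.0267 − 1.96 = 1.79; power 96%. With both at 60% it is 86%. A 5-point awareness margin would give only 47% at 80%.

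**The case against.** The strongest reply is that failing the rule does no lasting harm: a stakeholder conference follows, and even a winner is only a candidate. That stands. A tied procedure is discussed, not discarded. The defect is that the route to the conference is then taken largely by chance.

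The criteria are introduced as general lines, and the ranking wording could be read as not significantly lower; an unseen analysis plan might say so. This is possible. But the same section asks for significance on satisfaction and not here, so bare ranking is the plain reading, and leaving the choice until data are seen is the risk. A policy of accepting no loss of consent would also be legitimate, but the protocol does not state one.

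Three stronger inferences are not supported.

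- A reader might infer that opt-out plus can hardly ever be selected, because handing out opt-out forms will raise objections. At 0.5% or 1% non-consent against 0.1%, the consent pass rate does fall to 15% or 1.7%. Those rates are not in the protocol, which plans 0.1% for both arms. Its 4.6% counts questionnaire respondents who would withhold or were unsure, not returned opt-out forms.
- A reader might infer that the rule often names the wrong procedure on preference. With true preferences of 38/37/25 the second-ranked procedure meets the preference criterion in 32% of trials, but that one-point gap is assumed, is close to a tie, and covers one criterion out of several.
- A reader might infer that the winner can be beaten across the board. It cannot: preference rank, consent and awareness are all compared with both others. Only satisfaction, and the size of the preference gap, look at the lowest alone.

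The 82% and 65% also run against the hypothesis stated beside them in Sample size, statistical power, and may be transposed. If so, the roles of the two active arms swap and the gap in the rule remains.

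**Conclusion.** The point holds in three parts.

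1. Consent and awareness are fixed as rankings with no margin where the protocol expects ties. Read literally, a truly tied opt-out plus meets both in about 37% of trials. This rests on the protocol's 0.1% non-consent, an assumed common awareness of 80%, and independence of the two criteria. The awareness level hardly matters; the consent pass rate falls if the shared non-consent rate is higher.
2. The satisfaction criterion can be met by a procedure significantly below another one. This follows from the wording; the worked figures only illustrate it.
3. The satisfaction measure in the rule is not the primary outcome, and the control arm is at a disadvantage on it.

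The arm estimates and planned comparisons are unaffected, and the conference limits the harm. This should be fixed, but it does not undermine the trial.

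**What to change.** Amend Outcomes before data are seen.

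- **Consent and awareness:** require the lower 95% confidence limit of candidate minus each other arm to lie above a pre-specified negative margin. The sponsor should choose and justify each margin. For consent it should be smaller than the 10-point loss that the protocol calls relevant. The 5 points (consent) and 10 points (awareness) used above are illustrations. With events as rare as 0.1%, name a score-type or exact interval.
- **Satisfaction:** use satisfaction with the consent procedure, significantly above the lowest and not significantly below the other. Make the matching wording change for clinicians.
- **Comparisons:** Basic plan of analysis lists informed consent versus opt-out plus, and opt-out plus versus opt-out. Add informed consent versus opt-out, which the rule needs if informed consent is the candidate.

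The preference criterion can stay. Requiring a significant lead over the runner-up would be a trade-off, since near-ties would go to the same conference.

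Cost: agreement on the margins and a short change of wording. No extra patients are needed at the illustrative margins (power above 99% for consent at 1% versus 0.1% non-consent, 96% for awareness at 80%), but a much tighter awareness margin would be underpowered.

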## ***Patients and methods***

### **Study sample**

The study sample will be composed of 1800 patients, evenly distributed over the three study arms. Sample size is based on an expected response rate (for the questionnaire) of 75%. We will include patients who undergo surgery or biopsy (1600 patients) or blood drawing (200 patients). The former category of patients will contain patients who have a skin condition, a colorectal condition or a condition in the head/neck area. We include patients with malignant and non-malignant conditions of the same tissues or organs with a ratio of about 3:2, dependent on availability in each hospital. The absolute number of patients with specific conditions will also depend on the availability of these patients in the four hospitals. In the VUmc we will not include patients with (malignant and benign) colorectal conditions and malignant head/neck conditions, because almost all of them will also be asked to participate in a biobank (String of Pearls Initiative), which might confuse patients about what they are asked to give consent for. In the NKI-AVL, only patients with malignant conditions will be included. Figure 1 gives an overview of the number of patients in each of the groups in the four hospitals.

We will include patients between the ages of 18 and 80 years. There are two reasons for the upper age limit. First, we have learned from experience that patients over 80 are much less likely to be able or willing to complete questionnaires. Second, and more importantly, the two community hospitals in our study treat more patients over 80 than the two academic hospitals. Including these patients would mean that it would be difficult to determine whether any differences observed between patients from these different types of hospitals should be attributed to age differences or other causes.

Patients should be able to speak and read Dutch and have a sufficient mental capacity to complete the questionnaires by themselves. Patients will be included in the study by their treating physician or nurse practitioner.

### **Study design including study arms**

In this multicentre randomized controlled trial, 1800 patients will be recruited from academic and community hospitals during an 18 month period (Figure 2). The consent procedures will be offered a short time before or after the tissue or blood is removed, dependent on what is the best timing according to the clinician or nurse practitioner. Patients to be included are

distributed over four hospitals: two academic hospitals and two regional hospitals: the NKI-AVL, the Vrije Universiteit Medical Center (VUmc), the Spaarne hospital in Hoofddorp and the Kennemer hospital in Haarlem. Inclusion of academic and community hospitals will increase the external validity (i.e. generalizability) of the study results.

Patients will be randomized, stratified by hospital and diagnosis, to opt-out plus, informed consent or opt-out (control group) in collaboration with [name] (statistician NKI-AVL). Clinicians and nurse practitioners who will carry out the intervention will receive envelopes that each contain the paperwork (checklist, brochure in opt-out plus and informed consent arms and return envelopes) for one patient. The envelopes will be put in order of the randomization. Clinicians and nurse practitioners will write down his or her name, the patient's name, patient number, diagnosis, date and method of tissue removal on the checklist. A random selection of diagnoses on the checklists will be compared with the diagnoses in the medical files to check their validity. If the validity is found to be poor, all diagnoses will be checked.

In our previous intervention study (see preliminary results) we asked patients informed consent before the start of the intervention. However, patients felt that it was confusing to be asked informed consent for a study in which they were asked to provide informed consent. To prevent this kind of confusion in the current study, we will not ask consent for the randomization and the intervention. We believe that not asking consent for the randomization is suitable to our study because the informed consent procedure bears no potential harm to the participants, the intervention is of importance for future clinical research, the intervention includes no invasive procedure for the participants, and at least the standard care is offered to participants in the control group.

After the intervention, we will include an informed consent form in the first questionnaire. With this form, we ask consent for the first and second questionnaire (see below). At the end of the questionnaire permission will be asked for a telephone interview.

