## ***List of attachments***

- A: Detailed information on the background of this study and on previous research
- B: First questionnaire
- C: Second questionnaire
- D: Pre-intervention questionnaire medical staff
- E: Post-intervention questionnaire medical staff
- F: Brochure opt-out plus intervention arm
- G: Brochure informed consent intervention arm
- H: Information leaflet Tissue Issue
- I: Consent form Tissue Issue
- J: Patient letter 1
- K: Patient letter 2
- L: Patient reminder 1
- M: Patient reminder 2
- N: Inserted sheet with pictures of brochures
- O: Checklist medical staff informed consent
- P: Checklist medical staff opt-out plus
- Q: Checklist medical staff opt-out

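### The staff who include patients hold the ordered envelopes, and the first described record of a patient is the arm-specific form inside, so the arm can be known before a patient is committed

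*Protocol*

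**What the plan says.** All places are in the protocol.

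- **Who includes patients** (Study sample): "Patients will be included in the study by their treating physician or nurse practitioner".
- **Who holds the allocation** (Study design including study arms): "Clinicians and nurse practitioners who will carry out the intervention will receive envelopes that each contain the paperwork" for one patient. On their arrangement: "The envelopes will be put in order of the randomization".
- **What is inside** (same section): "checklist, brochure in opt-out plus and informed consent arms and return envelopes". The control envelope therefore has no brochure. The List of attachments gives each arm its own checklist: O for informed consent, P for opt-out plus, and for control "Q: Checklist medical staff opt-out".
- **Where the patient is recorded** (same section): staff enter their own name and "the patient's name, patient number, diagnosis, date and method of tissue removal on the checklist".
- **Consent to randomisation** (same section): "we will not ask consent for the randomization and the intervention".
- **Checks** (same section): a random sample of the diagnoses on the checklists is compared with the medical files. No other check of the checklists is described.

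The visible text does not mention sealing, opacity, numbering on the outside, central registration, or a log of eligible patients or unused envelopes.

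**The concern.** Randomisation protects a comparison only if the decision to include a patient is fixed before anyone can see the arm. Here the people who make that decision hold the sequence. Using an envelope is, in effect, the whole enrolment step, because patients are not asked to consent to being randomised. A member of staff could open the next envelope, see the arm, and then decide whether the patient in front of them is the one to include.

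There are reasons why staff might not be indifferent. The two active arms call for a verbal explanation, while control is usual care. Hypothesis 5 expects staff to prefer opt-out and opt-out plus. Inclusion also leaves room for judgement, since patients must have enough mental capacity to complete the questionnaires.

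At stake are the patient outcomes that feed the decision rules under Outcomes. Two of those rules (awareness, and consent rates for research) ask only that a procedure do no worse than the others, with no margin, so even a small shift between arms could matter to them.

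**Working it through.** No figure in the plan is in dispute. The check is a reading of the described steps, followed by illustrations on stated assumptions.

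**1. Order of events as described**

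| Step | Described in | Arm visible? |
|---|---|---|
| Clinician or nurse practitioner identifies a patient | Study sample | No |
| Consent to randomisation | Study design: not asked | – |
| Registration or log entry | Not described | – |
| Envelope taken from the ordered stack and opened | Study design (opening is implied) | Yes |
| Patient's name and number written on the checklist | Study design; attachments O, P, Q | Yes |

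The first described act that commits a patient comes after the arm can be seen. Sealing alone would not change this, because a sealed envelope can be opened before the patient is chosen. Recording the patient before opening would change it.

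**2. What the analysis could repair**

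Stratification is by hospital and diagnosis. The Basic plan of analysis adjusts for background variables on which the groups differ. Both act on measured characteristics only. Trust and attitudes to research, plausible drivers of selection, are collected in the first questionnaire, six weeks after the intervention, so they are not baseline covariates.

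**3. Illustration for consent rate**

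Inputs: 10% non-consent with informed consent and 0.1% with either opt-out procedure (Sample size, statistical power). Assumption: staff pass over a share s of would-be non-consenters in the informed consent arm only.

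Observed non-consent = 0.10(1 − s) / (1 − 0.10s)

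- s = 0.10: 0.090/0.990 = 9.1%
- s = 0.25: 0.075/0.975 = 7.7%
- s = 0.50: 0.050/0.950 = 5.3%

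At s = 0.50 the gap from 0.1% falls from 9.9 to about 5.2 points. Power (two-sided 0.05, continuity correction) is

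Φ{[|p1 − p2| − 1/n − 1.96√(2p̄(1 − p̄)/n)] / √[(p1(1 − p1) + p2(1 − p2))/n]}.

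For 5.26% versus 0.1%:

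- n = 450 per arm: 99.6%
- n = 150: 68%, against 96% with 10% versus 0.1%
- n = 90: 39%, against 77%

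So the main contrast survives even the extreme case. Subgroups of 90 to 150, the sizes the protocol mentions, would lose power.

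**4. Illustration for another binary outcome, with no true arm effect**

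Assumptions, none from the protocol: half of the patients have a 90% outcome rate and half 60% (overall 75%). Staff skip a share s of the lower-rate half in one arm. The higher-rate half then makes up w = 0.5/[0.5 + 0.5(1 − s)] of that arm, whose rate is 0.9w + 0.6(1 − w). The last column uses the power formula above without the 1/n term, at n = 450 per arm.

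| s | Rate in that arm | False difference | Chance of a significant result in that direction (nominal 2.5%) |
|---|---|---|---|
| 0.10 | 75.8% | 0.8 points | about 5% |
| 0.20 | 76.7% | 1.7 points | about 8% |
| 0.30 | 77.6% | 2.6 points | about 15% |
| 0.50 | 80.0% | 5.0 points | about 44% |

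With assumed rates of 80% and 50% the last column is about 4%, 8%, 13% and 36%.

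**The case against.** **The protocol does not say that staff see the arm in advance.** A clinician may settle on the patient, take the next envelope and complete the checklist, all consistently with the text. This stands. A reader might infer that the arm is in fact known beforehand. The text supports only that it can be known.

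**A safeguard may exist out of sight.** Figure 2 and attachments O to Q are not shown and could hold handling instructions. This stands as a limit on the finding. It does not remove the gap in the section that sets out the procedure.

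**Selection would not always go unseen.** Each checklist carries a staff name, a patient number and a date. An envelope held back for another patient would leave dates out of sequence, provided the order is retained. This stands for envelopes used out of order. It does not cover an opened envelope that is simply used for the next patient. The planned baseline comparison might also reveal gross selection on measured characteristics.

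**The motive is modest and points in no single direction.** The standardised text takes about a minute. On time alone staff would avoid both active arms, whereas Hypothesis 5 has them favouring opt-out plus. This stands, so no direction of bias can be claimed.

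**The consent-rate scenario is demanding.** Staff would have to foresee who will not post back a form. Such selection would also shrink the contrast and so work against Hypothesis 4. This stands, and the figures are illustrations only.

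**Not every arm comparison is exposed.** A reader might extend the point to all primary outcomes. Medical staff's satisfaction and preference do not compare randomised patients and fall outside it.

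**Conclusion.** The point holds as a weakness in the described procedure. It is not evidence that selection occurs. The staff group that includes patients holds the ordered envelopes, the contents and forms differ by arm, and no consent or registration step is described before the arm-specific checklist. Selection after seeing the arm is therefore possible, and the patient-level comparisons of consent rate, satisfaction, preference and awareness are open to bias that adjustment for measured variables cannot remove.

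The direction and size of any bias cannot be derived from the document. The 9.1%, 7.7% and 5.3% figures and the false-positive rates rest on assumed skipping shares and, for the latter, on assumed subgroup rates. They do not show that the main consent-rate conclusion would be overturned: at 450 per arm it would survive the most extreme case examined.

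How allocation is concealed is trial conduct that the protocol itself sets out, so the matter cannot be left to a statistical analysis plan. The conclusion assumes that the material not shown contains no registration step before opening. This is a cheap improvement that should be made.

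**What to change.** In the protocol, under Study design including study arms, state that:

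1. Envelopes are sealed, opaque, sequentially numbered and of equal bulk within each stratum, with blank sheets in the control envelopes.
2. The patient number and date are written on the outside of the envelope, or on a numbered log, before it is opened.
3. Every patient so recorded is analysed in the allocated arm.
4. Skipped, unused and out-of-order envelopes are returned and reported by arm and hospital.

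If Figure 2 or the staff checklists already contain such steps, bring them into this section. The second item matters most, because sealing without prior recording leaves the gap open. The cost is filler paper, a short log at each clinic and a few seconds per patient. Sample size and analysis methods need not change.
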